The proposed study responds to recent calls for more research into social prescribing (e.g., in the 2021 QLD Parliamentary Inquiry into social isolation and loneliness, the 2020 Royal Australian College of General Practitioners / Consumers Health Forum Round Table report, and the 2020 Friends for Good More than Medicine report). It also addresses the need for high-quality evidence to evaluate social prescribing in an Australian context. We will evaluate the effectiveness of social prescribing, in comparison to GP treatment as usual (TAU), in reducing loneliness, as well as its effects on wellbeing and health service usage across an 8-week period.

We hypothesise that participants who participate in social prescribing will show significant improvements in loneliness and wellbeing and lower use of health services relative to those in the TAU condition. Second, the study will test the processes through which observed outcomes occur, with a focus on evaluating the two pathways in the expanded SIMIC-based model to determine whether number of important social groups, new group identification, old and new group identity compatibility, and group-based psychological resources (support given and received, and emotion regulation) are implicated in reduced loneliness and health service use and increased wellbeing over the course of the study.

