## Methods

### Design and participants

While a randomised controlled design would be the strongest methodology, it requires participants to be interested and available to attend sessions with a link worker and then group activities as part of the social prescribing intervention if they are allocated to the treatment condition. It would be difficult to retain participants in social prescribing who are not interested and/or available, and conversely, it would be unethical to withhold social prescribing from participants who are interested and available, given evidence that it is potentially effective in managing loneliness. Accordingly, as shown in Fig. 2, our study will have a non-randomised controlled (parallel) design, with a social prescribing condition (SP) and a primary care treatment as usual (TAU) condition.

This research will take place in 5 sites in Southeast Queensland where social prescribing is offered, using a combination of GP and community centre models. The sites are in areas with diverse populations in terms of socioeconomic and cultural backgrounds: a community centre in a southern suburb of Brisbane, a GP clinic in the same suburb, a GP clinic in a southwestern suburb of Brisbane, a community centre in a northern suburb of Brisbane, and a combined GP and community centre in a regional city located about an hour’s drive south of Brisbane.

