*Social Prescribing participants* (SP) will be adults aged 18 and over, experiencing loneliness or social isolation who are eligible for referral to the social prescribing programs at these sites. Local General Practitioners and Allied Health Professionals expected to be the most likely referral pathway. Recruitment will be promoted through the authors giving talks to referring agents and through project steering meetings. Participants will have sufficient English language skills to be able to provide consent to participate in the research. We expect them to range in age, and to represent a variety of cultural and ethnic groups. Exclusion criteria are that the individual reports acute symptoms (such as suicidal ideation, manic or agitated behaviour, or intoxication), or an acute social issue (such as domestic violence or housing crisis that would need to take priority), that would interfere with their capacity to engage with SP. Such individuals will be directed by the Link Worker to a more suitable service. Link Workers will refer clients who indicate an openness to participating the study to the researchers who will contact individuals to confirm their consent to participate in the study.

*Treatment as Usual participants* (TAU) will be selected from GP clinics in the same locations as the social prescribing programs and will meet our inclusion and exclusion criteria. A staff member within each of these services will identify frequent attending patients who will be contacted by telephone by the researchers and invited to participate in the study. Frequently attending patients will be defined as patients attending the practice 12 or more times each year over a two-year period who have not already been referred to a social prescribing scheme. These parameters remove patients attending frequently for short-lived medical needs, such as a pregnancy. We will assess for baseline differences between the conditions and statistically control for any variables that are found to differ significantly at baseline.

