### Measures

***The primary outcomes are loneliness, wellbeing, and health service use, and these will be assessed in both T1 and T2 surveys.***

*Loneliness* will be assessed via the 8-item brief UCLA Loneliness Scale [45] (e.g., ‘how often do you feel left out?’), in which responses are made on a 4-point scale (where 0 = *never*, 1 = *rarely*, 2 = *sometimes*, and 3 = *often*). Items are summed to produce a total score ranging from 0 to 24.

*Wellbeing* will be measured using the 14-item Warwick Edinburgh Mental Wellbeing Scale [46]. The items are positively worded and ask respondents how often they have experienced various psychological states over the past 2 weeks (e.g., ‘I’ve been feeling relaxed’) on a 5-point rating scale (where 1 = *none of the time* to 5 = *all of the time*). Scores are summed to produce a total score in the range from 14 to 70, with higher scores corresponding to a higher level of mental well-being. The WEMWBS is psychometrically robust in general populations, with excellent internal consistency (α = 0.91) and good test-retest reliability (*r* = .83) [46].

*Health Service Use* will be measured by the self-reported total number of visits that participants make to hospital, community mental health services, counsellor, psychologist, psychiatrist, social worker, GP (in person, over the phone, or via home visit) over the course of the study (adapted from the measure used in [47]). In addition, respondents will be asked to rate their current health on a single 5-point scale (where 1 = *very poor* to 5 = *very good)*.

Secondary outcomes are process measures by which the social prescribing intervention is expected to produce effects on the primary outcomes: group memberships and identities, new group identification, former and new group compatibility, and group-based psychosocial resources of social support and emotion regulation.

*Group memberships and identities* Participants will be asked to list up to six groups that they are members of and rate the importance of each on a 7-point scale (where 1 = *not important* to 7 = *very important).* From this, the number of important groups (i.e., those rated 5–7) will be derived (see [34], p. 350–351).

*New group membership and identification* Social identification with the (first) new group that the participant has joined through the social prescribing program will be measured by 4-items rated on a 5-point scale (where 1 = *strongly disagree* to 5 = *strongly agree* [48];).

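### Only the TAU arm is selected on past GP attendance, and the planned baseline adjustment would not remove the resulting gap in health service use

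*Protocol article*

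**What the plan says.** The protocol article (Design and participants) states that "our study will have a non-randomised controlled (parallel) design, with a social prescribing condition (SP) and a primary care treatment as usual (TAU) condition". The two arms are then filled by different routes.

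- **SP:** adults "experiencing loneliness or social isolation who are eligible for referral to the social prescribing programs at these sites". No attendance threshold is given.
- **TAU:** patients who "will be selected from GP clinics in the same locations as the social prescribing programs and will meet our inclusion and exclusion criteria". They are found as follows: "A staff member within each of these services will identify frequent attending patients who will be contacted by telephone by the researchers". The definition is: "Frequently attending patients will be defined as patients attending the practice 12 or more times each year over a two-year period". The reason given is to leave out people who attend often for a passing medical need.

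Under Measures, "The primary outcomes are loneliness, wellbeing, and health service use, and these will be assessed in both T1 and T2 surveys". Health service use is the "self-reported total number of visits that participants make to hospital, community mental health services, counsellor, psychologist, psychiatrist, social worker, GP" over the study period, so GP visits enter the total directly. The Background hypothesises "significant improvements in loneliness and wellbeing and lower use of health services relative to those in the TAU condition".

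The one safeguard stated against baseline imbalance closes Design and participants: conditions will be compared at baseline, and variables that differ significantly will be controlled for. The Power calculation names a 2 x 2 mixed analysis of variance. The Analysis section names mixed-effects repeated measures models with timepoint, participant and condition.

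**The concern.** Giving up randomisation brings ordinary confounding, which the protocol acknowledges and explains. Choosing one arm on past values of a component of a primary outcome is a further step, and the reason given does not cover it. Leaving out short-lived need explains the two-year window, but not why only TAU is filtered.

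The safeguard is poorly matched to the problem. The arms are separated by two years of attendance. The variable that would enter the model is self-reported visits at T1 over a window of weeks or months. Adjusting for a noisy measure of the trait used for selection removes only part of the difference. What remains points the same way as the hypothesis, towards lower use in SP. A reader of a T1-adjusted result could not tell an SP effect on this outcome from the recruitment rule.

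**Working it through.** **1. The plan's own figure.** For f = 0.30 and N = 90, a two-group comparison at a single time point has noncentrality N x f² = 90 x 0.09 = 8.1 on 1 and 88 degrees of freedom. Power is 0.804, so the stated 90 reproduces. For two equal groups d = 2f = 0.60. The point below does not affect this calculation.

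**2. What the filter fixes.** Twelve visits a year is 12/4 = 3.0 per 3 months, or 12 x 56/365.25 = 1.84 per 8 weeks. Each TAU patient averaged at least this over the qualifying years. SP has no such floor. The floor is historical and does not bind T1 or T2.

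**3. Size under stated assumptions.** The documents give no attendance rates, so these are assumed: each person has a stable GP visit rate drawn from a gamma distribution with mean 4 to 12 a year and shape 1 or 2; counts are Poisson given the rate; TAU has 12 or more in both prior years; SP is unselected on attendance; there is no treatment effect. Results are GP visits per 8 weeks.

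| Mean, shape | TAU | SP | Gap (SD) | SP minus TAU after T1 adjustment |
|---|---|---|---|---|
| 4, 1 | 2.43 | 0.61 | 1.30 | -1.38 |
| 4, 2 | 2.01 | 0.61 | 1.13 | -1.20 |
| 6, 1 | 2.83 | 0.92 | 1.14 | -1.29 |
| 6, 2 | 2.36 | 0.92 | 1.00 | -1.13 |
| 8, 1 | 3.19 | 1.23 | 1.01 | -1.14 |
| 8, 2 | 2.65 | 1.23 | 0.87 | -1.05 |
| 12, 1 | 3.86 | 1.84 | 0.80 | -0.92 |
| 12, 2 | 3.19 | 1.84 | 0.67 | -0.84 |

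The unadjusted gap of 0.67 to 1.30 SD exceeds the 0.60 for which the trial is sized. T1 adjustment leaves between 0.92/(3.86 - 1.84) = 46% and 1.20/(2.01 - 0.61) = 86% of it.

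**4. Adjusting for the two-year count.** In this model the expected rate given a two-year total H and a T1 count t over w years is (shape + H + t)/(shape/mean + 2 + w). This is linear in H and t. Selection depends only on the yearly counts behind H, so once H and t are in the model, arm carries no further information. The residual gap is zero in theory and about zero in simulation.

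**5. Condition-by-time.** With stable rates, the expected T1 and T2 counts over equal windows are the same within each arm, so the level gap cancels. Suppose instead that T1 looks back 3 months, as the Abstract says, and that this window falls inside the second qualifying year. TAU is then caught partly on a high run. In the simulation the mean count in that year exceeds the true rate by 15.44 - 13.15 = 2.29 visits (4, 2) at most and 25.71 - 25.17 = 0.54 (12, 1) at least. Divided by 4, TAU would fall by about 0.14 to 0.57 visits per 3 months without any treatment, which counts against SP.

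**The case against.** The strongest reply is that the planned models are repeated-measures models, and the Discussion frames the expected loneliness and wellbeing effects as change between assessments. In a condition-by-time contrast a stable level gap cancels, and any fall in TAU attendance works against SP. This stands. A reader might infer that lower use in SP is guaranteed by the filter. The documents do not support that, because the direction depends on the contrast and on whether T1 visits are a covariate. The article does not name the decisive contrast (an analysis plan may), and its adjustment rule leads towards T1 adjustment, where the bias favours SP.

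Three further replies have weight.

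- Requiring high attendance in each of two years selects persistent attenders, which limits regression.
- SP referrals are expected mainly from GPs and allied health professionals, so some SP participants may attend often too. This would narrow the gap, and a complete lack of overlap should not be inferred.
- Practice visits are only one component of the outcome.

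A reader might also infer that SP gains in loneliness and wellbeing are inflated because people are referred at a peak of loneliness. The documents do not establish such a peak. TAU must meet the same inclusion criteria, and the Abstract describes all ninety participants as lonely.

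**Conclusion.** The point holds for health service use, one of three primary outcomes. The selection rule differs between the arms by design and acts on a component of that outcome, and the stated safeguard is inadequate for it. Under the assumptions in the working, T1 adjustment leaves a false SP advantage of about 0.8 to 1.4 GP visits per 8 weeks. A condition-by-time contrast is about unbiased with stable rates and biased against SP if TAU attendance regresses.

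The one-sided rule is a fact of the document. The size is illustrative. It rests on assumed attendance rates and on SP being unselected on attendance, and it would shrink if referred SP patients are themselves frequent attenders. The sample size and the loneliness and wellbeing outcomes are not called into question here.

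**What to change.** - Obtain for each SP participant the same two-year attendance count that defines TAU eligibility: from practice records, or by self-report where the participant came through a community centre (two of the five sites are community centres only). Record the actual count in TAU as well, not just that the threshold was met.
- Include this count in the health-service model, by covariate adjustment or overlap weights, regardless of any baseline significance test. If it is a covariate in the repeated-measures model, include its interaction with time; a main effect alone barely alters the condition-by-time estimate.
- State the condition-by-time contrast as the decisive one for this outcome.
- Report the comparison among SP participants who also meet the threshold as a sensitivity analysis. As the main analysis it could fall well below the planned 45 in that arm.
- Show the distribution of the two-year count by arm, and limit the conclusion on health service use if overlap is poor.

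The cost is one extra data item and some loss of precision. Self-reported two-year counts will contain error, so adjustment will be less complete where records are unavailable.

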Research interrogating the social cure approach has contributed to development of the social identity model of identity change (SIMIC) [34, 39], which specifies the group processes that support health and well-being in the context of life change (e.g., transitions to university study, parenthood, recovery from illness). This model argues that life transitions typically entail a loss of social group memberships and related social identities, and that, other things being equal, this will tend to compromise wellbeing. At the same time, though, SIMIC argues that in the context of life transitions, multiple group memberships and associated identities are generally protective of health and wellbeing. This is because having access to multiple group memberships (a) increases people’s ability to maintain some of these in the context of the transition (and thereby have a sense of social identity continuity) and (b) provides them with a platform for developing new group memberships (and thereby have a sense of social identity gain) and should thereby increase people’s access to health-supporting psychosocial resources. This should be more true to the extent that different group memberships are compatible as this makes them easier to manage and less stressful [40, 41].

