## Discussion

This project will represent the first controlled evaluation conducted in Australia - a country where such prescribing is only emerging [20, 21]. It will also be one of the few studies that adopts a social cure theoretical framework [33, 34] to understand the processes through which social prescribing to community group activities produces expected changes in loneliness, wellbeing, and health service use (see also [23, 38] in the UK). The wide range of self-report measures and link worker collected service data will provide a rich data set. Specifically, between the two assessments, we expect to find improvements in well-being and reduced loneliness among those engaging with the intervention, and minimal change in these outcomes for participants in the TAU condition.

In line with social cure theorising, and our extended SIMIC-based model of social prescribing, we expect improvements associated with joining a new group activity through social prescribing to be mediated by new group identification, old and new group compatibility, and group based psychological resources which are gained. These changes are expected to contribute to reduced health service use at follow-up, as has been observed in previous research in which adults who frequently attend GP clinics met their social needs through meaningful group participation [10].

The findings will be disseminated via a final report, a summary communicated to the participants and stakeholders by email, and in scholarly publications and presentations. They will inform policy and practice developments in the community and health sectors in Queensland and potentially have impact across Australia and beyond. This research is timely, as there have been growing calls for policy- and evidence-based interventions to address social isolation and loneliness, especially in the wake of the COVID-19 pandemic and related social distancing and lockdowns [51–54]. The absence of high-quality evidence and a rigorous theoretical framework is the primary barrier to wider implementation of a social prescribing approach and this study fills both of those gaps.

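### SP and TAU are recruited under different rules on persistence of need, so their untreated 8-week course in loneliness and wellbeing may differ and be read as an SP effect

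*Protocol article*

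**What the plan says.** All of the following is in the protocol article.

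- **Allocation** (Design and participants): "our study will have a non-randomised controlled (parallel) design".
- **SP entry** (same section): adults "experiencing loneliness or social isolation who are eligible for referral to the social prescribing programs at these sites". No minimum duration of loneliness or need is given. Under Data collection, the T1 survey is taken when the person first engages with the programme.
- **TAU entry** (Design and participants): "patients attending the practice 12 or more times each year over a two-year period who have not already been referred" to social prescribing. The stated purpose is that "These parameters remove patients attending frequently for short-lived medical needs, such as a pregnancy".
- **Shared criteria** (same section): TAU patients also "will meet our inclusion and exclusion criteria". The exclusions cover acute symptoms "or an acute social issue (such as domestic violence or housing crisis that would need to take priority"), where these would interfere with engaging in SP.
- **Adjustment** (same section): the analysis will control for variables found to differ significantly at baseline.
- **Measures**: loneliness, wellbeing, health service use and the group-process scales are described. Duration of loneliness and recent life change are not.
- **Expected result** (Discussion): improvement in SP and "minimal change in these outcomes for participants in the TAU condition".

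**The concern.** In a non-randomised comparison of change, the TAU arm has to show what would have happened to SP participants without SP. The authors saw short-lived need as a problem and screened for it in TAU, but put no matching rule on SP. Someone who moved to the area within the past two years would generally fail the TAU attendance rule but could enter SP. A new parent or a newly ill person could enter TAU only if already a frequent attender.

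The trial's own theory makes this relevant to the outcomes. The Background describes a model of wellbeing "in the context of life change (e.g., transitions to university study, parenthood, recovery from illness") and treats the loss of group memberships as a determinant of loneliness. If people in recent transition are more common in SP, and if their loneliness moves differently over 8 weeks, part of the difference in change between SP and TAU is natural course. Loneliness and wellbeing, two of the three primary outcomes, would both be affected. ITT and per-protocol analyses deal with missing data and adherence, so neither removes such a difference.

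**Working it through.** **1. The plan's own figure.** Inputs from Power calculation: f = 0.30, power 0.8, alpha 0.05, 45 per arm. For two equal groups d = 2f = 0.60. A two-group F test with noncentrality f² × N = 0.09 × 90 = 8.1 and 1 and 88 degrees of freedom has power 0.804, and 90 is the smallest even N reaching 0.80. The stated 90 reproduces and is not disputed. It supplies the yardstick of 0.60 SD.

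**2. Does the text create different rules on persistence?**

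| | SP | TAU |
|---|---|---|
| Need | Lonely or isolated, eligible for referral | Shared inclusion criteria plus frequent attendance |
| Persistence | None stated | 12 or more visits a year over two years |
| When surveyed | First engagement | Over the same 8-week interval, after identification from attendance history |
| Acute exclusions | Yes | Yes |

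Yes, on persistence of attendance. No rule in either arm acts directly on how long the person has been lonely.

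**3. Would the planned adjustment remove it?** Not reliably. A variable that is not measured cannot be adjusted for. If it were measured, a significance screen with 45 per arm can miss a real imbalance. Equal T1 scores can also go with different later courses.

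**4. Size.** The documents give no input for this, so everything here except the 45 per arm is assumed.

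Bias = (share recent-onset in SP − share in TAU) × excess unaided improvement in baseline SD.

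Set A: shares of 20–50% in SP and 0–10% in TAU, unaided improvement of 0.3–0.5 SD.
- Low: (0.2 − 0.1) × 0.3 = 0.03 SD. High: (0.5 − 0) × 0.5 = 0.25 SD.
- With a T1–T2 correlation of 0.6, SE of the difference in change = √(2 × 0.4) × √(2/45) = 0.189 SD.

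| Bias (SD) | Two-sided rejection rate with no SP effect |
|---|---|
| 0 (equal shares) | 5.0% |
| 0.03 | 5.3% |
| 0.10 | 8.3% |
| 0.15 | 12.5% |
| 0.25 | 26.3% |

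At 0.03 SD about 68% of the false positives favour SP (3.6% against 1.7%). At 0.25 SD nearly all do.

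Set B, wider: share difference of 10–50%, excess improvement of 0.5–1.0 SD.
- Bias = 0.1 × 0.5 = 0.05 SD to 0.5 × 1.0 = 0.50 SD.
- The SP change variance is raised for the mixture by p(1 − p)s², where p is the share difference and s the excess improvement.
- The chance of a significant result favouring SP (nominally 2.5%) is about 4% to 61% at correlation 0.5, 5% to 80% at 0.7 and 6% to 94% at 0.83. The last value is the test–retest figure quoted for the wellbeing scale under Measures.

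If recent-onset cases worsen over 8 weeks, the sign reverses and the bias runs against SP.

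**The case against.** A reader might infer that TAU has been filtered for long-standing loneliness, so that recent-onset loneliness enters mainly SP and biases the result in its favour. The strongest case against that reading has five parts.

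- **The filter is on medical attendance.** A two-year frequent attender who has just been bereaved or has just become lonely still qualifies for TAU. This stands. The arms differ by construction in duration of attendance, and a difference in duration of loneliness is an inference.
- **Both arms exclude acute symptoms and acute social issues.** This stands in part. It removes some transient crises, but only those that would interfere with engagement, so ordinary life transitions remain.
- **The Abstract links social prescribing to persistent health problems, and the Background points to disadvantage, disability and chronic illness.** This argues against an SP arm dominated by transient cases, but neither is an entry criterion.
- **Nothing in the documents says loneliness eases unaided within 8 weeks.** This stands. The Background says transitions tend to harm wellbeing, not that it soon recovers. The expected minimal change in TAU is the authors' forecast, not evidence about how TAU was selected.
- **A condensed article may not list every baseline item.** This is fair, so the point is limited to the measures the article describes. Even with those items collected, the rule of adjusting only for significant differences would remain.

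**Conclusion.** The concern holds in a limited form. The arms are drawn by different rules on persistence of need, allocation is not randomised, and the described measures and adjustment rule cannot be relied on to remove a difference in untreated course. An SP–TAU difference in change on loneliness or wellbeing could therefore be partly natural course.

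A bias favouring SP is plausible but not established. It needs two things the documents do not show: more recent-onset loneliness in SP than in TAU, and unaided improvement within 8 weeks. On assumed inputs the bias ranges from negligible (0.03 SD, rejection rate 5.3%) to close to the design effect (0.50 SD against 0.60 SD). With equal shares in both arms it is zero. The case for acting is that the remedy is cheap and would show whether the imbalance exists.

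**What to change.** 1. Add two short items to the T1 survey in both arms: how long the person has felt lonely, and whether a major life change (such as a birth, move, bereavement, new illness or job loss) occurred in the past 12 months. Report both by arm.
2. Prespecify both, each with its timepoint interaction, as covariates in the loneliness and wellbeing models, whether or not they differ significantly at baseline.
3. Prespecify a sensitivity analysis limited to participants in both arms whose loneliness has lasted more than 12 months.
4. State that, if the arms overlap poorly on these items, the SP–TAU difference in change may partly reflect different natural course.

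The restricted analysis should not replace the main one. Switching after seeing the overlap would be data-driven. It would also cost power: if half of SP were recent-onset, about 22 SP participants would remain against 45 in TAU, and power for d = 0.60 would fall from 0.80 to about 0.62 under the two-group test that reproduces the 90.

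Cost: two survey items, protocol wording and two more covariates with their interactions. Power is lower in the sensitivity analysis. Anyone already enrolled will have no T1 data on these items, which matters because the trial was registered retrospectively. With poor overlap the covariate adjustment rests on extrapolation, hence step 4.

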### Power calculation

An a priori power analysis indicates that a sample size of 90 would be required to detect a significant difference between groups with a medium effect size (*f* = .30) on primary outcome variables, with a power of 0.8 and a default alpha of .05, using the planned 2 X 2 mixed analysis of variance. Our goal for recruitment is therefore to continue until we reach 90 with data at both time points (i.e., 45 in each condition).

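### Adjustment variables are to be chosen by baseline significance in a non-randomised comparison, so moderate imbalances (observed, below about 0.42 SD at 45 per arm) go unadjusted whatever their prognostic weight.

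*Protocol article*

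**What the plan says.** Under Design and participants, the protocol article explains why randomisation was rejected and states that "our study will have a non-randomised controlled (parallel) design". The two arms come from different sources. SP participants are adults "experiencing loneliness or social isolation who are eligible for referral to the social prescribing programs at these sites". TAU participants are frequent attenders at GP clinics in the same locations: "Frequently attending patients will be defined as patients attending the practice 12 or more times each year over a two-year period".

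Confounding is dealt with in one sentence of the same section: the arms will be checked for differences at baseline, and the authors will "statistically control for any variables that are found to differ significantly at baseline". The level of the baseline test is not given. The Analysis section describes mixed-effects repeated measures models built on timepoint, participant and condition. It names no covariate and no matching or weighting.

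The Power calculation section plans to "continue until we reach 90 with data at both time points (i.e., 45 in each condition"), for a "medium effect size (*f* = .30) on primary outcome variables", "with a power of 0.8 and a default alpha of .05".

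**The concern.** The arms are formed by referral and self-selection on one side and by attendance records on the other. Systematic differences are therefore expected, and statistical adjustment carries most of the weight of the between-arm claim.

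The stated rule decides what enters the model by a significance test. With about 45 per arm, such a test can pass over a prognostic variable with a moderate imbalance and admit an irrelevant one that differs by chance. What matters for bias is the product of imbalance and prognostic strength, and the rule ignores the second factor. The primary model is also not fixed until the baseline data have been tested. The rule applies to all three primary outcomes: loneliness, wellbeing and health service use.

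**Working it through.** **Inputs from the article:** 45 per condition with data at both timepoints, f = 0.30, power 0.8, alpha 0.05 (Power calculation); WEMWBS test-retest correlation 0.83 (Measures).

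**Assumptions:** baseline tests are two-sided at 0.05; 45 per arm at baseline; confounder-outcome correlation r = 0.5 to 0.6; T1-T2 correlation rho between 0.5 and 0.83, the upper value borrowed from the retest figure.

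**1. The plan's own sample size.** For a two-group F test with noncentrality N × f² = 90 × 0.09 = 8.1, power is 0.804; at N = 88 it is 0.795. So 90 reproduces as a simple two-group comparison, and the target is d = 2 × 0.30 = 0.60.

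**2. Smallest imbalance that triggers adjustment.** This is t(0.975, 2n − 2) × √(2/n).
- n = 45: 1.987 × √(2/45) = 0.419 SD
- n = 50: about 0.40 SD
- n = 60: about 0.36 SD

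**3. Chance that a true imbalance escapes the rule** (noncentral t, 45 per arm).

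| True imbalance | Not significant |
|---|---|
| 0.2 SD | 84% |
| 0.3 SD | 71% |
| 0.4 SD | 53% |
| 0.5 SD | 35% |

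**4. Bias in the planned contrast.** The plan has two timepoints and its hypotheses concern improvement relative to TAU. Take an unadjusted observed imbalance of 0.4 SD, just under the threshold, in a variable with correlation r1 with the outcome at T1 and r2 at T2.
- Change contrast: bias = 0.4 × (r2 − r1). If r1 = r2, this is 0.
- T1-adjusted estimate with r1 = r2 = r: bias = 0.4 × r × (1 − rho).
  - rho = 0.83: 0.4 × 0.5 × 0.17 = 0.034 and 0.4 × 0.6 × 0.17 = 0.041 SD. Divided by 0.60, this is 6% to 7%.
  - rho = 0.5: 0.4 × 0.5 × 0.5 = 0.10 and 0.4 × 0.6 × 0.5 = 0.12 SD. Divided by 0.60, this is 17% to 20%.
- A variable that predicts change (r2 differs from r1) gives more than these values if the difference is large enough. The documents hold no figure for it.

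**5. Type I error.** A simulation of a single follow-up comparison (8,000 trials per setting, one confounder, true imbalance 0.3 to 0.4 SD, r = 0.5 or 0.7) gave 5.7% to 6.3% under the significance rule, against 4.5% to 4.9% when the variable was always adjusted for.

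**The case against.** A reader might infer that a missed 0.4 SD imbalance passes in full into each primary result, as 0.4 × 0.5 = 0.20 to 0.4 × 0.6 = 0.24 SD, or 33% to 40% of d = 0.60. The documents do not support that as a general figure. It is the bias of an unadjusted follow-up-only comparison, whereas the Power calculation and Analysis sections plan a repeated-measures analysis. There, a variable related equally to T1 and T2 cancels or shrinks as shown. Nor is it the average result of missing a true 0.4 SD imbalance, because the observed imbalance in those cases tends to be smaller. A reader might also infer that interval coverage fails badly. For one confounder the effect is modest, about 6% type I error against 5%, although several imbalances in the same direction could add up.

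The rule will also usually catch large imbalances. At 45 per arm a true difference of 0.8 SD is detected 96% of the time and one of 1.0 SD 99.7%. The baseline sample may exceed 45 per arm, which lowers the threshold. The article does not say that non-significant variables are excluded, and a full covariate list is commonly left to an analysis plan.

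These limits on size stand. They do not defend the rule itself. The article states a selection criterion rather than leaving one open, and that criterion is a poor one for a design without randomisation.

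**Conclusion.** The point holds as a weakness in a stated rule, not as a complaint about missing detail. Choosing confounders by baseline p-value leaves observed imbalances below about 0.42 SD unadjusted (0.36 SD at 60 per arm), and it misses a true 0.4 SD imbalance about half the time. These figures rest on an assumed two-sided 0.05 level and on the baseline arm size.

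The effect on the primary results is conditional. It ranges from nothing, through 6% to 20% of the planned effect with T1-adjusted estimation under the assumed correlations, to more for variables that predict change. The plan cannot know in advance which case applies. For that reason the choice of variables should rest on subject-matter grounds and be fixed before baseline results are examined.

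**What to change.** Replace the significance rule with a short list of pre-exposure confounders, named in advance on subject-matter grounds and included in every primary model whatever their baseline p-values. Candidates are site or locality, self-rated health, baseline loneliness and prior service use, plus age and sex if collected from individuals. The article mentions demographic characteristics only for the non-identified service audit, so this needs checking.

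- **Handle the T1 outcome once:** either as a timepoint in the repeated-measures model or as a covariate in a T2 model. If T1 stays as a timepoint, enter the confounders with their interaction with time; a main effect alone leaves the change contrast untouched when data are complete.
- **Leave out the T1 number of important groups,** or use it only in a sensitivity analysis. It is a process measure, and the Data collection section allows T1 to be taken after an SP participant has begun a group, so adjusting for it could remove part of the effect.
- **Describe balance with standardised differences** instead of p-values. A propensity-weighted sensitivity analysis is optional.

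The cost is wording and several degrees of freedom. Five sites take 4; self-rated health, loneliness, service use, age and sex take 5; a separate T1 outcome covariate, as for wellbeing, takes 1. That is about 10 of roughly 88, and fewer if sites are grouped by locality. If age and sex are not already collected, they must be added to the T1 survey.
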